### Treatment

In the treatment arm, eplerenone was initiated on the day of randomisation at 50 mg orally once daily. The dose of 50 mg once daily is the recommended dose in patients with heart failure. Carriers are maintained at this target dose, or the maximum tolerated dose, until the end of the study. Serum potassium and estimated glomerular filtration rate (eGRF) are monitored at the start of the study, 1–2 week(s) after study start and yearly, and these measures are documented together with the other investigations and vital parameters. The dose is reduced if needed, i.e. in case of hyperkalaemia (serum potassium > 5.5 mmol/l). Carriers undergo yearly follow-up in the cardiology outpatient clinic at each participating centre following routine clinical care. Physical examination, blood sampling (when treated with eplerenone), electrocardiogram, Holter monitoring and ergometry are performed every 12 months. CMR imaging and SA-ECG are performed at the start and end (36 months) of the study (Tab. 2).

**Table 2 Tab2:** Overview of study procedures

	Visit 1 start	Visit 2 1 week	Visit 3 1 year	Visit 4 2 years	Visit 5 3 years
Visit to outpatient clinic	*✔*	**–**	*✔*	*✔*	*✔*
History and current status	*✔*	**–**	*✔*	*✔*	*✔*
Physical examination	*✔*	**–**	*✔*	*✔*	*✔*
Electrocardiogram	*✔*	–	*✔*	*✔*	*✔*
Echocardiogram	*✔*	–	*✔*	*✔*	*✔*
Holter monitoring	*✔*	–	*✔*	*✔*	*✔*
Ergometry	*✔*	–	*✔*	*✔*	*✔*
Signal-averaged ECG	*✔*	–	–	–	*✔*
CMR	*✔*	–	–	–	*✔*
Blood analysis	*✔*	*✔*^a^	*✔*^a^	*✔*^a^	*✔*

Note: Subjects undergo several investigations as summarised in this table. They are requested to visit the outpatient clinic at baseline and at 1‑year intervals thereafter. Subjects randomised to eplerenone visit the outpatient clinic or their general practitioner after 1 week to check serum potassium and eGRF, which are also checked in these subjects at the yearly visits. Of note, all investigations except blood analysis are already performed as part of routine clinical care, which routinely includes evaluation of signs and symptoms of DCM and ACM. For the purpose of the study, we collect and use these available data.

*ECG* electrocardiography, *CMR* cardiac magnetic resonance, *eGFR* estimated glomerular filtration rate, *DCM* dilated cardiomyopathy, *ACM* arrhythmogenic cardiomyopathy

^a^ only for subjects randomised to eplerenone

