### Study endpoints

The primary and secondary endpoints are listed in Tab. 3. The primary endpoint is a multiparametric assessment of disease progression defined as a responder-based composite primary endpoint (Tab. 3). If one of the predefined parameters of the composite primary endpoint is reached, CMR imaging is performed and study end date recorded. After a follow-up period of 3 years, outcomes will be assessed by an independent adjudication committee blinded to the allocated group. In case of a favourable trend (but no significant effect as yet), the DSMB may advise continuing the study for 2 more years (“adaptive design”).

**Table 3 Tab3:** Primary and secondary endpoints

*Primary endpoint*^a^
LV end-diastolic volume, increase > 10% (assessed with CMR)
LV ejection fraction, absolute decrease > 5% (assessed with CMR)
RV end-diastolic volume, increase > 10% (assessed with CMR)
RV ejection fraction, absolute decrease > 5% (assessed with CMR)
Late enhancement, absolute increase > 5% (assessed with CMR)
QRS voltage, decrease > 25% (ECG, measured in I, II and III in mV)
Occurrence of non-sustained ventricular tachycardia (Holter monitoring, exercise testing)
Heart failure signs and/or symptoms or arrhythmias necessitating medical treatment according to the guidelines and likely due to arrhythmogenic cardiomyopathy
*Secondary endpoints*
All individual components of the primary endpoint
Diagnosis of DCM (according to Mestroni criteria [19])
Diagnosis of ARVC (according to revised task force criteria [18])
Development of global or regional dysfunction and structural alterations (according to revised task force criterion 1 [18])
QRS axis (12-lead ECG)
Conduction intervals (PR interval, QRS duration [12-lead ECG; SA-ECG])
STT segment changes (12-lead ECG)
Change in biomarkers
Occurrence of sustained ventricular tachycardia or ventricular fibrillation
Hospitalisation for a cardiovascular reason

*LV* left ventricular, *CMR* cardiac magnetic resonance*, RV* right ventricular,* ECG* electrocardiogram,* DCM* dilated cardiomyopathy, *ARVC* arrhythmogenic right ventricular cardiomyopathy,* SA-ECG* signal-averaged electrocardiography

^a^The primary endpoint is a multiparametric assessment of disease progression defined as a responder-based composite primary endpoint. If one of the predefined parameters of the composite primary endpoint is reached, CMR imaging is performed and study end date recorded

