### Sample size estimation

This clinical trial was designed based on the assumptions that 50% of the presymptomatic PLN p.Arg14del carrier group without treatment will reach the primary endpoint within 3 years and that treatment with eplerenone is expected to reduce this percentage by 50%. To ensure at least 80% power to detect a difference between the control group and the eplerenone group, at a significance level of 0.05, 128 carriers (64 in each group) are needed. To account for 10–15% loss to follow-up during the study, we aimed to include 150 subjects.

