### Statistical analysis

After completion of the study, all eligible carriers who have been randomised to the treatment arm and received at least 1 dose of eplerenone will be used in the analyses of the primary and secondary efficacy endpoints, as well as in the safety analysis. Safety will be assessed by summarising the incidence and type of adverse events and the changes in laboratory parameters. The proportion of carriers experiencing serious adverse events and the proportion of carriers with noteworthy changes in laboratory parameters will be compared between treatment groups. The analysis of primary endpoints and secondary endpoints will be performed according to their assigned treatment group in accordance with the intention-to-treat principle. Additional analysis sets may be used in exploratory analyses. The number of subjects withdrawing from the study will be tabulated by their reasons for withdrawal and by treatment group. Potenzial biases due to withdrawal of subjects will be investigated. Baseline characteristics will be compared using chi-squared test (or Fisher’s exact test if appropriate). If differences are found, caution will be exercised when interpreting the results of the analyses between groups and methods may be modified to adjust for this difference.

The primary outcome will be presented by Kaplan-Meier curves for the treatment group, followed by the stratified log-rank test using stratification variables. Multivariate analysis will also be used to compare the endpoints between the two groups, adjusting for other variables including sex, age and screening centre. For missing data, the last observations made will be used. Unless stated otherwise, all secondary analyses will be performed using the same subjects included in the primary analysis. Secondary variables will be analysed using an appropriate statistical test, depending on the nature of the variable. Changes in parameters over time in the different treatment groups will be analysed using repeated measurement analysis or techniques that evaluate the timing of endpoints, when appropriate. For all tests, a *p*-value < 0.05 is considered statistically significant. Statistical analysis will be performed in SPSS (IBM SPSS Inc., Chicago, IL, USA; newest version at moment of analysis).

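### The Kaplan-Meier and log-rank analysis stated for the primary outcome fits neither a composite detected mainly at the month-36 scan nor the continuous components that have since replaced it

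*Protocol article*

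**What the plan says.** All references are to the protocol article.

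- **Statistical analysis:** "The primary outcome will be presented by Kaplan-Meier curves for the treatment group, followed by the stratified log-rank test using stratification variables". Randomisation and blinding names centre as the stratification factor.
- **Study endpoints, Table 3:** the composite is a yes/no responder endpoint with eight components. Five are CMR measures: LV and RV end-diastolic volume, LV and RV ejection fraction, and late enhancement. The others are QRS voltage, non-sustained ventricular tachycardia on Holter or exercise testing, and treated heart failure or arrhythmia.
- **Treatment:** "CMR imaging and SA-ECG are performed at the start and end (36 months) of the study". ECG, Holter and ergometry are yearly (also Table 2).
- **Study endpoints:** "If one of the predefined parameters of the composite primary endpoint is reached, CMR imaging is performed and study end date recorded". This is the only statement about a date, and it does not say which date counts as the event time.
- **Sample size estimation:** the assumption is that "50% of the presymptomatic PLN p.Arg14del carrier group without treatment will reach the primary endpoint within 3 years", halved under eplerenone, with 64 per group.
- **Baseline results:** recruitment stopped at 84 (42 per group). The components will now be analysed on a continuous scale in place of the dichotomous composite, and the analysis plan was amended. The Abstract (Methods), Study endpoints and Discussion still name the composite as primary. The Discussion adds that its assessment will be adapted.

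**The concern.** Kaplan-Meier and the log-rank test need a time for each event. A CMR component can be a participant's first event only at the final scan, because an earlier scan follows only when some other component has already been met. QRS voltage and Holter or exercise findings surface at yearly visits. Only treated heart failure or arrhythmia can carry a true date. The composite is therefore mostly a status found at a visit.

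If each participant's recorded date is used, event-free participants are censored at their own final visit, inside the same few weeks in which most events are logged. The denominator then shrinks for a reason unrelated to progression. At stake are the reading of the curve, some power, and clarity about which analysis is primary. Continuous changes in volume or ejection fraction have no event time, so the stated method does not fit the amended assessment either.

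**Working it through.** **1. The plan's own figure.** Inputs from Sample size estimation: 0.50 v 0.25, power at least 80%, significance level 0.05 (two-sided assumed).
- Exact power of Fisher's test: 79.4% at 63 per arm, 80.2% at 64. The stated 128 reproduces as a comparison of proportions.
- Pooled z-test at n per arm: power = Φ[(0.25√n − 1.96√(2 × 0.375 × 0.625)) / √(0.25 + 0.1875)]. At n = 64: (2.000 − 1.342)/0.661 = 0.995, so 84.0%. At n = 42: (1.620 − 1.342)/0.661 = 0.421, so 66.3%.
- Log-rank under proportional hazards: HR = ln 0.75/ln 0.50 = 0.415. Schoenfeld gives 41 events; with a mean event rate of 0.375 that is about 110 participants. Freedman gives 46 events, about 123. Neither gives 128, though 128 covers both.

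**2. The curve with recorded dates.** Assume a true 3-year risk of 0.50, a share f of events found at months 12 or 24, the rest at month 36, and symmetric scatter of final-visit dates. After the early visits the curve stands at S = 1 − 0.5f. Of those left, a fraction q = 0.5(1 − f)/(1 − 0.5f) will be events at the final visit.
- *Read at exactly 36 months*, when half the final visits have passed: S ≈ (1 − 0.5f) × 0.5^q. For f = 0.1, q = 0.474: 0.95 × 0.720 = 0.684, so 32%. For f = 0.5, q = 0.333: 0.75 × 0.794 = 0.595, so 40%. Simulation gave 31-41%.
- *Read at its last point*, with m = n(1 − 0.5f) participants left: expected S = (1 − 0.5f) × ∏(1 − q/k), k = 1 to m. For f = 0.5, n = 42 (m ≈ 32): 0.75 × 0.232 = 0.174, so 83%. For f = 0.1, n = 64 (m ≈ 61): 0.95 × 0.084 = 0.080, so 92%. Simulation gave 82-92%.

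Both should be 50%.

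**3. Power, by simulation.** Same set-up, f from 0.1 to 0.5, visit dates scattered normally with SD 1 month, no dropout, no centre stratification. Repeat runs moved the figures by about two points.

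| Per arm | Log-rank, recorded dates | Test of proportions |
|---|---|---|
| 64 | about 67-77% | about 85% |
| 42 | about 47-59% | about 67% |

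A second model used exponential times, a 30/60/90% CMR share of the hazard, and final dates spread evenly over ±3 months. At 64 per arm, log-rank power was 79/75/67% and type I error 4.7-5.6%.

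**4. Nominal visit times.** With all final visits placed at month 36, the simulation in step 3 puts the log-rank about 1-3 points below the test of proportions. In the exponential model its power is about 85% at 64 per arm, equal to that with exact event times. With 75 per arm, 15% dropout and a 60% CMR share it is 85.5%, against 87.7% with exact times.

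The curve's shape before month 36 remains uninformative. With a CMR share s of the hazard, the control curve at year k shows 1 − 2^(−(1−s)k/3). For s = 0.6 that is 8.8% and 16.9% at years 1 and 2, against true values of 20.6% and 37.0%, followed by a step to 50%.

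**The case against.** The strongest reply is that Baseline results has already replaced the dichotomous composite and says the analysis plan was amended, so the log-rank analysis may no longer be the primary one. A journal article may also leave the event-date rule to that plan, and the rule decides how much harm there is: nominal times remove nearly all the power loss. This stands in part. It limits the size of the problem. It does not explain why Statistical analysis still gives, in the future tense, a method that suits neither form of the endpoint.

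A reader might infer three stronger things that the documents do not support.
- *That the sample size is wrong.* It reproduces for proportions. The shortfall to about 66% at 42 per arm with the test of proportions comes from recruitment.
- *That the log-rank test is invalid.* With the same schedule in both arms, type I error stays near 5%. Inflation to 10-27% appeared only when control visits were assumed to run two weeks late. Table 2 gives both arms the same yearly visits; the only extra contact under eplerenone is at week 1.
- *That visit dates are the stated event dates.* That is an inference.

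Two further limits are fair. Five of eight counts components, not events, and the share found early is assumed. The 82-92% and 31-41% depend on where the curve is read, which the article does not prescribe. Finally, Kaplan-Meier censors the expected 10-15% lost to follow-up, whereas a month-36 proportion needs a status for each of them.

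**Conclusion.** The point holds as a mismatch between the stated analysis and the endpoint, visit schedule, sample-size basis and amended assessment. If recorded dates are used, with SD 1 month scatter and 10-50% of events found early, the log-rank test gives up roughly 8-18 points of power at 64 per arm (85 − 77 to 85 − 67) and 8-20 at 42 (67 − 59 to 67 − 47), and the late part of the curve cannot be read as a 3-year risk. With nominal times the power cost is about 1-3 points, but the curve still says little about timing before month 36. The documents give no figure for the visit scatter or the share of events found early. The correction is worth making because it needs no new data.

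**What to change.** 1. Reconcile Statistical analysis, the Abstract (Methods), Study endpoints and the Discussion with Baseline results, so that the continuous components are the stated primary analysis.
2. For any retained analysis of the composite, compare the proportion reaching it by month 36 with a centre-stratified Mantel-Haenszel risk difference and test, which matches the sample-size basis. Alternatively, fit a discrete-time (complementary log-log) model on the nominal intervals 0-12, 12-24 and 24-36 months, or an interval-censored model, with centre as a factor. In the interval-censored model, progression first seen on the month-36 CMR could have occurred at any time since baseline. These models also accommodate dropout.
3. Keep Kaplan-Meier and log-rank for components with true dates, such as heart failure or arrhythmia needing treatment.

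**Cost:** wording only. The familiar curve is lost. The proportion analysis needs a stated rule for participants lost before month 36. The section's general last-observation rule does not settle this well: without an earlier triggered scan, the last CMR is the baseline one, so those participants would count as unchanged on five components.

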**Fig. 1 Fig1:**
[figure not shown]
Function of phospholamban. Phospholamban (PLN; *blue arrow*) is a reversibly phosphorylated transmembrane protein that binds to and regulates the activity of the sarcoplasmic reticulum Ca^2+^ ATPase (SERCA2a) pump. *From*: MacLennan et al. Nat Rev Mol Cell Biol. 2003 [27]. Printed with permission from Springer Nature

The clinical phenotype of PLN p.Arg14del carriers is characterised by malignant ventricular arrhythmias, sudden cardiac arrest and progressive heart failure [1, 3–5]. An experimental murine overexpression model of this PLN pathogenic variant found the cardiomyopathy to be characterised by progressive cardiomyocyte loss and severe cardiac fibrosis, and a similar phenotype was observed in a recently developed knock-in model that also recapitulated the clinical findings [6, 7]. Indeed, in our patients, we observed left ventricular myocardial fibrosis even in the presence of preserved (> 45%) left ventricular ejection fraction (LVEF), which suggests that tissue remodelling occurs early on in PLN p.Arg14del carriers, occurring even before onset of overt disease [1, 8, 9]. An earlier study by our group showed that an LVEF below 45% (rather than 35%, as in other types of cardiomyopathy) is an independent risk factor for ventricular arrhythmia in PLN p.Arg14del carriers [3]. We recently refined this observation, showing that left ventricular late gadolinium enhancement (LV-LGE) is an even stronger risk factor than LVEF. In fact, even when LVEF is preserved, LV-LGE appeared to be associated with a higher risk of ventricular arrhythmia in PLN p.Arg14del carriers [9].

Analogous to other inherited cardiomyopathies, the natural course of PLN p.Arg14del cardiomyopathy is age-related; after a presymptomatic phase of variable length, many PLN p.Arg14del carriers progress to overt cardiomyopathy. These patients are treated according to general clinical guidelines for these conditions.

Family cascade screening can, however, identify presymptomatic family members carrying the PLN p.Arg14del pathogenic variant, thereby providing a unique window of opportunity to initiate pre-emptive treatment in carriers before symptoms occur, potentially preventing sudden cardiac death or disease development and progression. However, no evidence-based treatment is currently available for presymptomatic carriers even though early treatment before the onset of any symptoms is potentially of major prognostic importance.

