### Randomisation and blinding

Central randomisation was conducted by the Trial Coordination Center of the University Medical Center Groningen (www.tcc.umcg.nl). Randomisation was stratified according to participating centres to ensure a similar sample distribution between the two test groups. According to the PROBE design, randomisation is blinded to the CMR core lab in the UMCG for assessment of the CMR images, which are performed as previously described [9]. An independent endpoint adjudication committee assesses the other primary and secondary endpoints.

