## Baseline results

In May 2014, the first participant was included into the study. Because of slow recruitment, in January 2018 it was decided to stop further inclusion of participants and complete the protocolled follow-up duration with the included cohort (*N* = 84). At this point, it had become clear that it was not realistic to assume that enough participants would be included to reach the originally defined composite primary endpoint (Tab. 3). Instead of a composite dichotomous endpoint, i.e. using the pre-specified cut-off values, individual components of the primary endpoint will now be analysed on a continuous scale to investigate possible significant differences. The statistical analysis plan was amended accordingly, and the decision to amend the study design, i.e. to stop inclusion of participants and to continue with the included cohort, was supported by the DSMB and the medical ethics committee. The primary objective remains showing that eplerenone retards disease progression. The majority of participants have now finished the study and the remaining participants are expected to finish in 2021.

An overview of the baseline characteristics of the 84 participants is provided in Tab. 4. By design, at baseline, all participants were in NHYA class I and had an LVEF > 45% and less than 2500 ventricular premature complexes (VPCs) during 24-hour Holter monitoring. Mean LVEF was 60% (±0.04). The median number of VPCs was 8 (0-1861). Baseline CMR scans were obtained for all 84 participants, but image quality was insufficient to perform adequate analyses in six cases. In the remaining 78 cases, as many as 14 cases (18%) showed LGE, mainly in the inferolateral left ventricular wall, suggestive of myocardial fibrosis. The six cases with insufficient image quality will be included for analysis of the other endpoints. An illustrative example is shown in Fig. 2. There were no statistically significant differences between the two groups in any of the baseline characteristics.

**Table 4 Tab4:** Baseline characteristics: no statistical differences between eplerenone and control group

	All	Eplerenone group	Control group
Number, *n*	84	42	42
Age at inclusion, years (SD)	39.5 (±13.1)	40.2 (±13.0)	38.8 (±13.4)
Male sex, *n* (%)	37 (44)	18 (43)	19 (45)
Body mass index, kg/m^2^ (SD)	25.7 (±4.8)	26.5 (±5.6)	24.9 (±3.6)
Systolic blood pressure, mm Hg (SD)	124 (±16)	128 (±17)	121 (±13)
Diastolic blood pressure, mm Hg (SD)	74 (±11)	75 (±10)	74 (±11)

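### Baseline LV-LGE, the risk marker that the article ranks above LVEF for ventricular arrhythmia, is not among the named adjustment variables, and the baseline-test rule would not bring it in

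*Protocol article*

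**What the plan says.** The Statistical analysis section of the Protocol article describes Kaplan-Meier curves "followed by the stratified log-rank test using stratification variables", and then a multivariate comparison "adjusting for other variables including sex, age and screening centre". Under Randomisation and blinding, the only stratification variable is centre: "Randomisation was stratified according to participating centres". So neither the stratified test nor the named covariates involve LV-LGE.

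The other route to adjustment is a test. Baseline characteristics are compared by chi-squared or Fisher's exact test, and if differences appear, "methods may be modified to adjust for this difference".

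On the marker itself, the Introduction (text after Fig. 1) reports from the group's own work that "left ventricular late gadolinium enhancement (LV-LGE) is an even stronger risk factor than LVEF", and that even with preserved LVEF "LV-LGE appeared to be associated with a higher risk of ventricular arrhythmia in PLN p.Arg14del carriers". Table 1 notes that LGE does not exclude a carrier. In Baseline results, of 78 readable scans, "as many as 14 cases (18%) showed LGE". Table 4 splits these as 9 (22%) on eplerenone and 5 (13%) on control. The same section concludes: "There were no statistically significant differences between the two groups in any of the baseline characteristics".

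**The concern.** A baseline covariate should be chosen because it predicts the outcome, and chosen before results by arm are known. The article supplies that evidence for LV-LGE in carriers with preserved LVEF, which is the trial population, and for an outcome that is part of the primary endpoint in Table 3 (non-sustained ventricular tachycardia, and arrhythmias needing treatment). Yet LV-LGE is not named. The rule that could add it asks whether the arms differ significantly at baseline. That question says nothing about prognosis, and with 14 positive carriers it will rarely be answered yes.

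Two things are at stake. One is precision, in a trial that stopped at 84 carriers against 128 needed. The other is credibility: the imbalance runs against eplerenone, most participants have finished, and treatment is open-label. If LV-LGE entered the model only after results were seen, a reader could fairly ask whether it was chosen for its effect on the answer.

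**Working it through.** **Inputs.** Table 4: LV-LGE in 9 and 5 carriers, 42 randomised per arm. Baseline results: 14 of 78 readable scans, six unreadable. The article gives no size for the effect of LV-LGE on any component, so that effect is an assumption here and is shown as a range.

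**Reproducing the article's figures.** 14/78 = 17.9%, printed as 18%. The arm denominators are not printed. They must sum to 78, and two splits come close to 22% and 13%:
- 41 and 37: 9/41 = 22.0%, 5/37 = 13.5%, difference 8.4 points.
- 40 and 38: 9/40 = 22.5%, 5/38 = 13.2%, difference 9.3 points.

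**Would the test rule bring LV-LGE in?** For 41/37, chi-squared p = 0.33 and Fisher p = 0.39. For 40/38, chi-squared p = 0.28 and Fisher p = 0.38. It would not.

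**Is the rule stable?** ECG repolarisation abnormality in Table 4, 13 of 42 against 5 of 42, gives p = 0.033 by uncorrected chi-squared and 0.061 by Fisher. The section names both tests, and the choice between them decides whether this row counts as a difference.

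**Size on a continuous component.** Let g be the assumed effect of LV-LGE on change, in within-group SD, and p = 14/78, so p(1 − p) = 0.147.
- Shift in the arm difference = g × (difference in LV-LGE prevalence).
- Standard error of the arm difference = √(2/42) = 0.218 SD.
- Variance explained = g²p(1 − p) / [1 + g²p(1 − p)].
- Gain expressed as extra participants = 84 × g²p(1 − p), before the degrees of freedom spent.

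| g (assumed) | Shift, SD | Shift / 0.218 | Variance explained | Extra participants |
|---|---|---|---|---|
| 0.25 | 0.021–0.023 | 0.10–0.11 | 0.9% | 0.8 |
| 0.5 | 0.042–0.047 | 0.19–0.21 | 3.6% | 3.1 |
| 0.8 | 0.068–0.075 | 0.31–0.34 | 8.6% | 7.9 |
| 1.0 | 0.084–0.093 | 0.39–0.43 | 12.8% | 12.4 |

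For scale, the difference detectable with 80% power at 42 per arm is (1.96 + 0.84) × 0.218 = 0.61 SD.

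**Size on an event scale.** If LV-LGE raises 3-year event risk by 20 to 40 points (assumption), the shift against eplerenone is between 0.20 × 8.4 = 1.7 and 0.40 × 9.3 = 3.7 points.

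The variance figures apply to linear models. In a Cox or logistic model the gain from a prognostic covariate appears as power for the conditional effect, not as a smaller standard error.

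**The case against.** The strongest reply is that nothing has been left out. The word that introduces the three covariates makes them examples, and Baseline results says that the statistical analysis plan was amended when the endpoint changed. That plan is not shown and may already name LV-LGE. This stands as far as it goes: the article cannot be read as closing the list or as excluding LV-LGE. What remains is that the article states both the variables and the rule for adding to them, and the rule is a poor one wherever the final list is written.

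A second reply concerns scope. The prognostic evidence is for ventricular arrhythmia. Most components in Table 3 are CMR or ECG measures, now to be analysed on a continuous scale, and the article gives no effect of LV-LGE on LVEF, volumes or QRS voltage. This stands. For those components the benefit is an assumption.

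A third is that singling out one row of Table 4 is selective. ECG repolarisation abnormality differs more, while median ventricular premature complexes (8 v 12) and LVEF (60% v 59%) lean slightly the other way. This also stands, and it is why the imbalance should not be the argument.

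A reader might infer from 22% against 13% that the comparison is biased against eplerenone. The documents do not support that. It is a difference of four carriers after randomisation, compatible with chance, and the error rate of the test already allows for such differences.

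**Conclusion.** The point holds in a limited form. The article names sex, age and centre in an open list and ties further adjustment to baseline testing. By that route, the marker it ranks above LVEF for arrhythmia would not be added. The case for adjusting is firm for the arrhythmia components and any time-to-event analysis that is kept, and rests on assumption for the other components.

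The size is modest. On a continuous component the conditional shift stays at about 0.4 standard errors or less and the variance explained at 13% or less, for assumed LV-LGE effects up to 1 SD. If LV-LGE does not predict a given component, there is almost nothing to gain there. These figures also depend on arm denominators inferred from rounded percentages. The point is worth acting on because the data are already held, recruitment is closed, and the choice carries weight only if made before outcomes are compared by arm.

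**What to change.** Before outcomes are compared by arm, check the amended statistical analysis plan. If it does not already do so, add a line that:

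- names baseline LV-LGE (present or absent, core-lab read) as a fixed covariate in the adjusted analyses, first for the arrhythmia components and any time-to-event analysis, and also for the other components apart from late enhancement itself;
- closes the covariate list and drops the baseline significance test as a route into it;
- uses a missing category for the six carriers with unreadable baseline scans, since Baseline results keeps them in the analysis of the other endpoints.

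The cost is one degree of freedom for LV-LGE and a second where the missing category is used. With few arrhythmia events, a category of six carriers may contain none, and its coefficient would then not be estimable. The plan should say how that is handled, for example by a penalised fit. No new data are needed.

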Known intolerance or contraindication for aldosterone antagonists
Participation in another drug trial in which the last dose of drug was within the past 30 days
Contra-indications for CMR (claustrophobia, metal devices)
Subjects unable or unwilling to provide written informed consent

Note: presence of late gadolinium enhancement on CMR is not an exclusion criterion

*PLN* phospholamban*, DCM* dilated cardiomyopathy,* LV* left ventricular, *ARVC* arrhythmogenic right ventricular cardiomyopathy,* RV* right ventricular,* eGFR* estimated glomerular filtration rate,* NSAIDs* non-steroidal anti-inflammatory drug*s, CMR* cardiac magnetic resonance

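### Carrying the last observation forward enters zero CMR change for participants lost without an endpoint-triggered scan, because baseline is the only earlier scheduled CMR

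*Protocol article*

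**What the plan says.** The Statistical analysis section states: "For missing data, the last observations made will be used". It makes no exception for any variable. The same section promises to tabulate withdrawals by reason and arm, to look into bias from withdrawal, and to use repeated-measures methods where suitable.

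On timing, the Treatment section says that "CMR imaging and SA-ECG are performed at the start and end (36 months) of the study", and Table 2 shows no CMR at 1 or 2 years. By contrast, "electrocardiogram, Holter monitoring and ergometry are performed every 12 months", and Table 2 adds a yearly echocardiogram.

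There is one route to an extra scan. Study endpoints and the footnote to Table 3 say: "If one of the predefined parameters of the composite primary endpoint is reached, CMR imaging is performed and study end date recorded".

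Five of the eight primary components in Table 3 are CMR measures: LVEDV, LVEF, RVEDV, RVEF and late enhancement. The Baseline results section moves the analysis from the dichotomous composite to the individual components on a continuous scale. It also reports that at baseline "image quality was insufficient to perform adequate analyses in six cases", leaving 78 of 84, and adds: "The six cases with insufficient image quality will be included for analysis of the other endpoints".

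**The concern.** Carrying a value forward assumes that nothing changed after it was recorded. For yearly measures that value is often a post-baseline one. For CMR, a participant who leaves before 36 months and has had no triggered scan has only the baseline scan to carry. Change is then baseline minus baseline, which is zero by construction. Under the dichotomous definition such a participant counts as not progressed on all five CMR components. Under the continuous analysis each zero goes straight into an arm mean.

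Zero is not neutral here. The Sample size estimation section expects half of untreated carriers to reach the endpoint within 3 years, so no change is on average better than the truth. The trial compares open-label eplerenone with no treatment, so the arms could plausibly lose different numbers. Blinded reading of the scans does not protect against this, because the bias comes from scans that were never made.

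**Working it through.** **The plan's own loss figure.** The plan needs 128 participants and, allowing for 10–15% "loss to follow-up during the study, we aimed to include 150 subjects". Check: 128 / 0.90 = 142.2 and 128 / 0.85 = 150.6, so 150 matches the upper end. The 64 per arm also reproduces: exact power of the two-sided Fisher test for 50% versus 25% is 79.4% at 63 per arm and 80.2% at 64. The sample size is not in question. The 10–15% is used below as the plan's expected loss, not as an observed rate.

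**How many zeros.** Among the 78 with a usable baseline scan, 78 × 0.10 = 7.8 and 78 × 0.15 = 11.7. About 8 to 12 participants would be entered as unchanged if none of those lost had a triggered scan.

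**Effect on the estimate.** Let *m* be the fraction of an arm whose final CMR is replaced by baseline, with loss unrelated to outcome, and let *μ* be the true mean change. The arm's analysed mean is (1 − *m*) × *μ* + *m* × 0 = (1 − *m*)*μ*.

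- *Equal loss.* The between-arm difference is multiplied by (1 − *m*): 0.90 at 10% and 0.85 at 15%. An assumed true LVEF difference of 2.5 points becomes 2.5 × 0.85 = 2.1. On the dichotomous scale, if the planned 50% versus 25% applied to a CMR-only responder endpoint, it would appear as 45.0% versus 22.5% at 10% loss, and as 42.5% versus 21.25% at 15%.
- *Unequal loss, no drug effect.* With the same true decline in both arms, the spurious benefit to eplerenone is (*m* on eplerenone − *m* in control) × decline.

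**Illustration of unequal loss.** Assumptions not in the documents: LVEF change SD 4 points, a 3-point decline in both arms, no drug effect, loss at random within arm, and the split of loss between arms. The 42 per arm is the number randomised. The test is a two-sided t-test at 0.05, and the last column is the simulated share of trials significantly favouring eplerenone.

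| Loss, eplerenone vs control | Spurious benefit (points) | Favourable false positives |
|---|---|---|
| 15% vs 10% | 0.05 × 3 = 0.15 | about 3.8% |
| 20% vs 10% | 0.10 × 3 = 0.30 | 5.4–5.7% |
| 20% vs 5% | 0.15 × 3 = 0.45 | 7.7–8.1% |

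The ranges are the spread between separate simulation runs. Analysing only the observed scans under the same random loss gives no bias and about 2.5%. Equal loss with no drug effect also leaves carry-forward at about 2.5%. The result depends on the assumed decline: with 1 point rather than 3, 15% versus 10% gives 0.05 × 1 = 0.05 points and about 2.9%.

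**The case against.** The strongest reply is that the rule does not score every missing final CMR as zero. That is correct. A participant who meets the QRS-voltage, non-sustained tachycardia, or symptom and arrhythmia criterion early should have a triggered CMR to carry forward. The six without an analysable baseline scan have no CMR change to compute and go only into the other endpoints. The point is confined to participants with a usable baseline scan and no triggered one.

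Two stronger readings are tempting, and the documents support neither.

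- *A reader might infer that carry-forward causes a marked loss of power.* With a true difference of 2.5 points (changes of −0.5 and −3), SD 4 and 15% loss in both arms, power is about 81% with complete data, 73% with carry-forward and 74% with observed scans only. Nearly all of the fall comes from the missing scans themselves.
- *A reader might infer that participants given a metal device, and so no longer scannable, would be recorded as stable progressors.* Table 1 lists metal devices only as an entry exclusion, and no implants are reported. A device needed for arrhythmia would probably follow an event that is itself a Table 3 component, which triggers a CMR and counts as progression.

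It can also be said that the plan promises to investigate withdrawal bias and to use repeated-measures methods. Neither replaces the rule, and a repeated-measures model fed with carried-forward values inherits the bias. Finally, the amended SAP is not shown and may say something else. That uncertainty stands: the section containing the rule still describes Kaplan-Meier curves and a log-rank test. Even so, the article reports the amendment and states no other rule for missing data.

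**Conclusion.** The concern holds for participants with a usable baseline CMR who are lost without an endpoint-triggered scan. For them the stated rule enters zero change on five of the eight primary components.

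The attenuation under equal loss, to 90–85% of the true difference at the plan's 10–15%, needs only the assumption that loss is unrelated to outcome. The direction of bias under unequal loss, towards the arm with more missing scans, follows from the same arithmetic provided the disease progresses on average.

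The absolute sizes are illustrations. Near the plan's own range (15% versus 10%) the distortion is small. It becomes material at 20% versus 5%, where favourable false positives are about three times the nominal 2.5%. The article gives neither the actual number of missing 36-month scans nor their split by arm, so the realised bias cannot be computed.

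**What to change.** For the CMR components, withdraw the carry-forward rule before the arms are compared. Replace it with a likelihood-based model, or with multiple imputation by arm, under missing-at-random. Use baseline values and the yearly ECG, Holter and echocardiogram results in Table 2 as auxiliary variables. Add one delta-adjusted sensitivity analysis in which missing CMR changes are made progressively worse than the imputed values, and report missing final scans by arm and reason. If the amended SAP already does this, it is enough to say so and to correct the sentence in the article.

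No new data are needed. The cost is a paragraph in the SAP and modest extra programming. The main analysis would also rest on a missing-at-random assumption, which cannot be verified and which the delta-adjusted analysis is there to test.
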